| Endpoints                  | 
The primary endpoint is the area under the concentration time curve in oxytocin level from baseline oxytocin measurement (before intake) to 6 hours after a single administration of MDMA (100mg) as compared to placebo in the same subjects between patients with central diabetes insipidus and healthy volunteers.
 
Secondary outcomes will be assessed between MDMA as compared to placebo for patients with central diabetes insipidus and healthy volunteers:
 
 
A. Peak change in OT plasma level
 
B. Time course of plasma OT levels
 
C. Time course of plasma MDMA concentration
 
D. Time course of cortisol, prolactin, copeptin and ACTH levels
 
E. Subjective/emotional effects assessed on a 10-point visual analog scale (e.g., feelings of anxiety, pleasure, fear, 0-10)
 
F. Recognition of negative emotions in the face emotion recognition task (FERT)
 
G. Empathy in the multifaceted empathy task (MET)
 
H. Anxiety level with the State-Trait Anxiety Inventory (STAI)
 
F. Level of Alexithymia using the Toronto-Alexithymia-Scale 20 (TAS-20)
 
G. Level of depression using the Beck-Depressions-Inventory II (BDI-II)
 
H. Level of general physical & mental health using the short form health survey (SF-36)
 
I. Safety: Assessments of clinical/laboratory variables (blood pressure, heart rate, body temperature, plasma sodium)
 
                                             |

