| Statistical Considerations | 
Hypothesis
 
The primary endpoint is the area under the concentration time curve in oxytocin level from baseline oxytocin measurement (before intake) to 6 hours after a single administration of MDMA (100mg) as compared to placebo in the same subjects between patients with central diabetes insipidus and healthy volunteers.
 
The null hypothesis is that the area under the concentration time of oxytocin is equal for patients with central diabetes insipidus and healthy volunteers after a single dose of MDMA, i.e. the primary endpoint is zero. The alternative hypothesis is that the area under the concentration time of oxytocin is lower in patients with central diabetes insipidus as compared to healthy volunteers, i.e. the primary endpoint is not zero.
 
Statistical Analysis
 
The primary endpoint, area under the concentration time curve for oxytocin will be analyzed for a difference from zero for patients with central diabetes insipidus and healthy volunteers. The p-value from the test will be reported.
 
The time course of oxytocin measures after intake of MDMA and placebo will be visualized by means of line plots and boxplots for patients with central diabetes insipidus and healthy volunteers. Summary statistics (median, interquartile range, minimum and maximum value) will be presented for each measurement time of oxytocin for MDMA and placebo for patients with central diabetes insipidus and healthy volunteers. Maximum oxytocin time will be
 |

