## 2 BACKGROUND AND RATIONALE

Disruption of the hypothalamic-pituitary axis due to congenital abnormalities, tumors or head trauma may cause anterior and/or posterior pituitary deficiency also known as partial or panhypopituitarism. Patients with hypopituitarism, especially those with panhypopituitarism (i.e., anterior and posterior deficiency) often report residual symptoms and lower quality of life (QoL) despite adequate substitution treatment of deficient pituitary hormones and often persists over several years of treatment and still does not reach population norms [1- 5].

The neuropeptide oxytocin (OT) is produced in the paraventricular nucleus and supraoptic nucleus of the hypothalamus and released into the circulation from the axon terminals that project to the posterior pituitary gland. OT is secreted in a pulsatile manner [6,7] is influenced by sex hormones, and socioeconomic functioning. It plays an important role during labour inducing uterus contraction, lactation and psychosocial functions, including attachment, pair bonding, socioemotional processing and parenting [8–15].

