#### **3.2. Primary and secondary endpoints**

The primary endpoint is the area under the concentration time curve in OT level from baseline OT measurement (before intake) to 6 hours after a single administration of MDMA (100mg) as compared to placebo in the same subjects between patients with central diabetes insipidus and healthy volunteers.

Secondary outcomes will be assessed between MDMA as compared to placebo for patients with central diabetes insipidus and healthy volunteers:

- A. Peak change in OT plasma level
- B. Time course of plasma OT levels
- C. Time course of plasma MDMA concentration
- D. Time course of cortisol, prolactin, copeptin and ACTH levels
- E. Subjective/emotional effects assessed on a 10-point visual analog scale (e.g., feelings of anxiety, pleasure, fear)
- F. Recognition of negative emotions in the face emotion recognition task (FERT)

- G. Empathy in the multifaceted empathy task (MET)
- H. Anxiety level with the State-Trait Anxiety Inventory (STAI)
- F. Level of Alexithymia using the Toronto-Alexithymia-Scale 20 (TAS-20)
- G. Level of depression using the Beck-Depressions-Inventory II (BDI-II)
- H. Level of general physical & mental health using the short form health survey (SF-36)
- I. Safety: Assessments of clinical/laboratory variables (blood pressure, heart rate, body temperature, plasma sodium)

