Blood samples: Samples will be collected on the study days as shown in Table 2. Blood will be collected to determine OT, MDMA and plasma sodium level at 0 min, 90 min, 120 min, 150 min, 180min and 300 min. Cortisol, prolactin, copeptin and ACTH concentrations will be taken at 0 min, 90 min, 150 min and 300 min. The blood samples will be taken as aliquots for the later batch analysis and will be centrifuged at 4°C at 3000 rpm for 10 min, and then stored at -80°C until analysis. Plasma sodium level will be taken for instant analysis. A basal hormonal status will be

conducted at baseline in main visit 1 at timepoint 0 min including TSH, fT4, IGF1, FSH, LH, Testosterone and Estradiol. Blood concentrations are determined in our laboratory using validated and previously used methods.

Amount of blood sampling: The total amount of blood collected during the study is 310 ml. This amounts to less than a standard blood donation and spread out over a time frame of 8 -10 weeks. The risk is there for acceptable for the participants.

Computer test: At timepoint 150 min during the expected peak concentration of MDMA participants will perform the following tasks: Face emotion recognition (FERT) and multifaceted empathy task (MET). The test will take 25 minutes in total for the participant. See section below for further information.

Standardized meal / fluid intake: The subject will be allowed to drink to thirst – the total fluid intake will be (in addition to 250ml i.v.) recorded during the main visit. We will offer a standardized breakfast and lunch at timepoint -60 min and timepoint 180 min.

End of session: Subjects will be under continuous medical supervision until any alterations of consciousness have completely subsided, this is expected within 6h for MDMA. After the test session subjects are allowed to leave only if the subjective effects have ceased (VAS score “drug effect” back to predose  $\pm$  1) and as assessed by the investigator. No close monitoring is needed beyond this time and subjects can return home as also was the case in a similar study [39, 43, 55].

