Subjects are prohibited to drive a car or to operate any machines within 48 h of substance administration. As for any complications resulting from this clinical study the investigators will provide assistance for treatment and the costs are covered by the study insurance. Any AE between sessions will be recorded at the beginning of the next session or telephone interview. Safety follow-up meetings beyond this time are not needed [57]. However, subjects will be provided with the phone number of the study physician, and the study leader in case they need assistance, or should medical problems arise.

Second main visit: After a washout-phase of at least 2 weeks, visit 2 will be scheduled. At Visit 2, participants will undergo the same procedure as described above with the second intervention. In female participants, the main visits will preferentially be planned during the mid-follicular phase or if on estrogen replacement therapy, during the active treatment phase

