## **5 STATISTICS AND METHODOLOGY**

### **5.1. Statistical analysis plan and sample size calculation**

The null hypothesis is that the area under the concentration time curve of OT is equal for patients with central diabetes insipidus and healthy volunteers after a single dose of MDMA, i.e. the primary endpoint is zero. The alternative hypothesis is that the area under the concentration time of OT is lower in patients with central diabetes insipidus as compared to healthy volunteers, i.e. the primary endpoint is not zero.

The time course of OT measures after intake of MDMA and placebo will be visualized by means of line plots and boxplots for patients with central diabetes insipidus and healthy volunteers. Summary statistics (median, interquartile range, minimum and maximum value) will be presented for each measurement time of OT for MDMA and placebo for patients with central diabetes insipidus and healthy volunteers. Maximum OT time will be summarized for MDMA and placebo for patients with central diabetes insipidus and healthy volunteers separately by means of frequency distribution according to the measurement times, and by median, interquartile range, minimum and maximum value. OT area under the concentration time curve from baseline to 6 hours after intervention will be tested for a difference between MDMA and placebo for patients with central diabetes insipidus and healthy volunteers. Summary statistics (median, interquartile range, minimum and maximum value) will be presented separately.

All other secondary endpoints will be analyzed descriptively. The time course of MDMA, cortisol, prolactin, copeptin, and ACTH levels will be visualized by means of line plots and boxplots, and summary statistics will be presented for each measurement time for MDMA and placebo for patients with central diabetes insipidus and healthy volunteers separately.

Sample size was estimated in order to show a significant increase in OT after the intake of a single oral dose of MDMA with a power of 90 % and a significance level  $\alpha$  of 0.05. Sample size estimation was based on preliminary data from 28 healthy adults. In this trial, OT levels following MDMA intake was studied. The mean increase in OT levels for MDMA was 809+/-64 pg/mL and 259 +/- 62 pmol for placebo.

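### The primary oxytocin AUC test is stated without a baseline term although 0-min oxytocin is drawn at both sessions; adjusting for the session difference could gain precision at almost no cost

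*Protocol*

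**What the plan says.** The synopsis (Endpoints) defines the primary variable in these words: "area under the concentration time curve in oxytocin level from baseline oxytocin measurement (before intake) to 6 hours after a single administration of MDMA". Section 3.2 completes the contrast: "as compared to placebo in the same subjects between patients with central diabetes insipidus and healthy volunteers".

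The synopsis (Statistical Considerations) states the analysis as follows: "area under the concentration time curve for oxytocin will be analyzed for a difference from zero". It also asks for the p-value. Section 5.1, whose heading includes the words statistical analysis plan, adds: "OT area under the concentration time curve from baseline to 6 hours after intervention will be tested for a difference between MDMA and placebo". Neither place mentions a baseline covariate, a baseline subtraction or an incremental AUC.

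Section 4.3.2 schedules "OT, MDMA and plasma sodium level at 0 min, 90 min, 120 min, 150 min, 180min and 300 min", and for the other session: "At Visit 2, participants will undergo the same procedure as described above with the second intervention". Every participant who completes both visits therefore has two pre-dose oxytocin values. Section 2 notes that "OT is secreted in a pulsatile manner".

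**The concern.** The primary answer compares patients with controls on a within-subject AUC difference, with 15 recruited and 12 evaluable participants per group (reading section 5.1's figures as per group, as the synopsis does). The placebo visit cancels whatever is constant in a person's basal oxytocin. It does not cancel the part that differs between the two visit days. The protocol itself gives reasons to expect such a part: pulsatile release, the influence of sex hormones, and cycle-phase scheduling that is only preferred. That part enters the AUC difference as noise.

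A pre-dose measure of it is already collected. If it predicts the AUC difference, leaving it out of the model gives a wider interval and a lower chance of detecting the assumed 30% reduction.

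**Working it through.** **The plan's own figures.** 12/(1 − 0.20) = 15 reproduces the step from evaluable to recruited. The 12 at 90% power does not reproduce for the patients-versus-controls comparison under the standard-error reading below, which needs about 41 per group (t-test, two-sided). Power is therefore computed at the stated group sizes.

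**Weight of the 0-min value in the AUC.** With samples at 0, 90, 120, 150, 180 and 300 min, the trapezoid rule gives the first point 90/2 = 45 min. Over the sampled 300 min that is 45/300 = 15%.

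**Inputs from section 5.1.** Mean increase 809 ± 64 (MDMA) and 259 ± 62 (placebo), from 28 healthy adults; 30% reduction assumed in patients.

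**Assumptions.** The ± is a standard error; both spreads are in the same unit (the text gives pg/mL and pmol); within-subject correlation 0.5; two-sided 5%. The correlation ρ between the 0-min session difference and the AUC session difference runs from 0 to 0.7.

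1. SDs: 64 × √28 = 338.7; 62 × √28 = 328.1.
2. SD of the within-subject difference: √(338.7² + 328.1² − 2 × 0.5 × 338.7 × 328.1) = 333.5.
3. Group effect: 0.30 × 809 = 242.7, so d = 242.7/333.5 = 0.728.
4. Unadjusted power: noncentral t with parameter d√(n/2) and 2n − 2 df. At n = 15 the parameter is 1.993 (28 df); at n = 12 it is 1.783 (22 df).
5. Adjusted power: replace d by d/√[(1 − ρ²)(1 + 1/(2n − 4))], with 2n − 3 df. Example, n = 15 and ρ = 0.5: 0.728/√(0.75 × 1.0385) = 0.825, 27 df.

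| n per group | unadjusted | ρ = 0 | ρ = 0.3 | ρ = 0.5 | ρ = 0.7 |
|---|---|---|---|---|---|
| 15 | 48.6% | 47.1% | 50.7% | 58.6% | 75.2% |
| 12 | 39.9% | 38.2% | 41.3% | 48.3% | 64.2% |

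Adjustment breaks even at ρ of about 0.2. With a within-subject correlation of 0.3 or 0.7 instead of 0.5, the gain at ρ = 0.5 is still about 7 to 10 points.

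**The standard-deviation reading.** The SD of the difference is √(64² + 62² − 64 × 62) = 63.0 and d = 242.7/63.0 = 3.85. Power is near 100% with or without the covariate.

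**Interval width.** The ratio of adjusted to unadjusted half-width does not depend on how ± is read. It is [t(2n − 3)/t(2n − 2)] × √[(1 − ρ²)(1 + 1/(2n − 4))]. For n = 15 and ρ = 0.5 this is (2.052/2.048) × 0.8825 = 0.88; for ρ = 0 it is 1.02.

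**Which baseline.** In a linear model the adjusted group difference equals the raw difference minus b times the group gap in the covariate mean, where b is the within-group slope.

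- *MDMA-day baseline alone.* If patients have basal oxytocin lower by g and the same response, the adjusted difference is 0 − b(−g) = bg, which is not zero when b is not. With b positive, this also offsets part of a real response deficit. Two simulations with assumed variances, lower basal oxytocin in patients and equal response gave 20% and 14.6% false positives.
- *Session difference.* It is measured before dosing, order is randomised and counterbalanced, and the protocol expects no residual effect after the washout. Its expected value is therefore zero in both groups and nothing is shifted. The same simulations gave 5.6% and 4.6%, against 5.1% and 5.3% unadjusted. The exact values depend on the assumed variances; the direction follows from the algebra.
- *Plain subtraction.* If the baseline difference has the same SD as the AUC difference on a time-averaged scale, the variance changes by the factor 2 − 2ρ. That is a loss whenever ρ is below 0.5, so subtraction is not a safe default.

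**The case against.** The strongest reply is that nothing here is wrong. The protocol does not name a test or a model, so it neither imposes an unadjusted analysis nor excludes a covariate, and such a choice is commonly made in a separate SAP. This stands against calling the point an error. It does not remove the point, because the protocol states its primary test in two places, one of them headed as the analysis plan, and a sentence there would settle it.

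A reader might infer that the 0-min data are ignored. They are not: the value is the first AUC point, with 15% of the sampled weight. A reader might also infer that the AUC is definitely uncorrected. Starting the curve at the pre-dose sample most naturally describes a time window, but it does not rule out an incremental AUC.

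A third inference is that power is being lost. The documents cannot show this. They give no correlation, and the pulsatility in section 2, with its doubts about single basal measurements, could mean that one pre-dose sample predicts the next hours poorly. Moreover, the section 5.1 figures are described as increases in level and not as AUCs. If they are changes from baseline, their spread may already exclude some of this variance, and the computed gain would be overstated. These limits stand.

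**Conclusion.** The point holds as an optional efficiency improvement. No baseline adjustment is stated for the primary AUC comparison, pre-dose oxytocin exists for both sessions, and session-to-session basal variation remains in the AUC difference.

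The size is conditional. Under the standard-error reading with a within-subject correlation of 0.5, the change at 15 per group runs from a loss of about 2 points (ρ = 0) to a gain of about 27 (ρ = 0.7), with 10 points at ρ = 0.5. Under the standard-deviation reading there is no power to gain, only a narrower interval if ρ is high enough.

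The documents do not support a claim that the primary test is invalid: the unadjusted comparison kept about 5% false positives in the simulations. The inflated rates belong to single-session adjustment, which the protocol does not propose. They matter only as a reason to name the right covariate in advance.

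**What to change.** In section 5.1 and the synopsis, state the primary analysis as a linear model of each participant's oxytocin AUC difference (MDMA minus placebo) on group (patient or control), with that participant's 0-min oxytocin difference (MDMA day minus placebo day) as covariate. Report the adjusted group difference with its 95% CI. State that neither session's baseline will be used alone as the covariate.

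The cost is a sentence or two and one degree of freedom. No extra samples are needed. If the covariate correlation is below about 0.2, the loss is at most about 2 points of power.

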### **3 STUDY OBJECTIVES AND DESIGN**

#### **3.1. Hypothesis and primary objective**

We hypothesize that OT provocation following a single dose administration of MDMA is reduced in patients with central diabetes insipidus as compared to healthy volunteers. The primary objective of this study is to evaluate OT levels in response to MDMA administration as compared to placebo in patients with central diabetes insipidus and healthy volunteers.

Secondary objectives are to evaluate physical and emotional changes between MDMA and placebo for patients with central diabetes insipidus and healthy volunteers:

- A. Evaluation of maximum OT peak following MDMA
- B. Time course of plasma OT levels
- C. Time course of plasma concentrations of MDMA
- D. Changes of other endocrine hormones
- E. Change of subjective feelings
- F. Change of mood perception
- G. Change of empathy
- H. Change in anxiety levels
- F. Change in alexithymia
- G. Change in depressed mood
- H. Change in general health status
- I. Safety measurements

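### The protocol states its primary comparison in several incompatible forms and does not fix which contrast, or which sidedness, is confirmatory

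*Protocol*

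**What the plan says.** Protocol section 3.1 sets a directional, between-group hypothesis: "OT provocation following a single dose administration of MDMA is reduced in patients with central diabetes insipidus as compared to healthy volunteers".

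Section 3.2, repeated in the synopsis, defines the primary endpoint as the oxytocin AUC from baseline to 6 hours on MDMA, "as compared to placebo in the same subjects between patients with central diabetes insipidus and healthy volunteers". That reads as a difference of differences.

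Section 5.1 and the synopsis give the null hypothesis as "area under the concentration time curve of OT is equal for patients with central diabetes insipidus and healthy volunteers after a single dose of MDMA". Placebo is not mentioned. The sentence then continues "after a single dose of MDMA, i.e. the primary endpoint is zero". The alternative is that the AUC "is lower in patients with central diabetes insipidus as compared to healthy volunteers, i.e. the primary endpoint is not zero".

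The synopsis states the primary analysis: the "area under the concentration time curve for oxytocin will be analyzed for a difference from zero for patients with central diabetes insipidus and healthy volunteers", with the p-value from the test to be reported. Section 5.1 does not repeat that sentence. The only test it names is that the AUC "will be tested for a difference between MDMA and placebo for patients with central diabetes insipidus and healthy volunteers".

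The sample-size text first gives its purpose as showing an increase in oxytocin after MDMA, at 90% power and alpha 0.05 with no sidedness. It then assumes a 30% lower level in patients than in volunteers.

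**The concern.** Three different contrasts are consistent with some part of this text:

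- (a) each group's AUC, or its MDMA-minus-placebo change, tested against zero;
- (b) patients versus volunteers on the MDMA day alone;
- (c) patients versus volunteers on MDMA minus placebo.

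Only (c) matches the endpoint in section 3.2. Contrast (a) shows whether MDMA raises oxytocin in each group, not whether the rise is smaller in patients. Contrast (b) mixes basal oxytocin with the response to provocation. Section 2 cites studies that found lower oxytocin in these patients, and one that did not, so a basal difference is plausible. The same data could therefore support different conclusions depending on which contrast is called primary, and the text does not prevent that choice after unblinding. The conflict between lower and not zero leaves the type I error in the hypothesised direction at either 5% or 2.5%.

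**Working it through.** **Inputs.** From the sample-size text in section 5.1: MDMA 809 ± 64 pg/mL; placebo 259 ± 62, printed as pmol; 28 healthy adults; 30% reduction; 12 evaluable and 15 recruited; 20% dropout. The synopsis gives 15 patients and 15 volunteers.

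**Assumptions not in the document.** Whether ± is an SD or a standard error (SEM); the within-subject correlation ρ; common units; equal SD in patients; levels standing in for AUC. As SEM, SD = 64√28 = 338.7 on MDMA and 62√28 = 328.1 on placebo.

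**1. The plan's own figure.** 12/(1 − 0.20) = 15 reproduces. The 12 does not identify the contrast. For contrast (b), difference 0.30 × 809 = 242.7, 90% power (normal approximation), the need is 2 per group if ± is SD. If ± is SEM it is 41 two-sided or 34 one-sided. The sample size therefore cannot settle which test was meant.

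**2. Contrast (a), MDMA minus placebo within each group, n = 12, two-sided 0.05 (t critical 2.20, 11 df).** SD of the difference = √(338.7² + 328.1² − 2ρ × 338.7 × 328.1) = 471.5 at ρ = 0 and 333.5 at ρ = 0.5. Noncentrality = increase × √12 / SD. The volunteer increase is 809 − 259 = 550.

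| Group and increase | ρ = 0 | ρ = 0.5 |
|---|---|---|
| Volunteers, 550 | 4.04 → 96% | 5.71 → 99.9% |
| Patients, increase 30% smaller (385) | 2.83 → 73% | 4.00 → 95% |
| Patients, MDMA level 30% lower (566.3 − 259 = 307.3) | 2.26 → 54% | 3.19 → 83% |

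The chance that both groups are significant, with patients at 385, is 0.956 × 0.731 = 70% to 0.999 × 0.953 = 95%. If ± is SD, then at ρ = 0 the SD of the difference is √(64² + 62²) = 89.1 and the patients' noncentrality is 385 × √12 / 89.1 = 15.0, so both groups reject almost always. On either reading, a positive result in both groups is the usual outcome even when the response is reduced.

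**3. Contrast (b), MDMA day only.** For illustration, take 259 as a level, give both groups the same 550 rise, and make the patients' placebo level 30% lower: shift 0.30 × 259 = 77.7. At 12 per group the two-sided test then rejects in 8% of trials (SEM reading) or 81% (SD reading), with no difference in response. The text calls 259 a mean increase. If it is one, these percentages do not apply, but the mixing of basal level and response remains, because the endpoint is an AUC of concentrations.

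**4. Sidedness, contrast (b), 15 per group, alpha 0.05 (28 df).** SEM reading: d = 242.7/338.7 = 0.717; noncentrality 0.717 × √(15/2) = 1.96; critical t 2.05 two-sided and 1.70 one-sided; power 47% and 61%. SD reading: d = 242.7/64 = 3.8, and power is near 100% either way.

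**The case against.** The best defence is that the text, read as a whole, intends contrast (c). Equating equal groups with a primary endpoint of zero makes sense only if the endpoint is itself the between-group difference, and section 3.2 defines it with placebo as reference. The synopsis speaks of one p-value from one test. It also lists the MDMA-versus-placebo test separately, so the primary test need not be that one. On this reading, testing for a difference from zero is correct. The word lower would then be the research hypothesis and not zero the formal two-sided alternative. A test procedure can be left to a statistical analysis plan, which was not available here.

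Much of this stands. A reader might infer that the protocol commits to testing each group's raw AUC against zero, so that the primary p-value is bound to be significant and the hypothesis goes untested. The document does not support that: it is one reading of an ambiguous sentence, and the less likely one. Section 5.1 also does state between-group hypotheses.

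The defence does not secure contrast (c), however. The null sentence has no placebo term. The synopsis analysis sentence shortens the endpoint to the plain oxytocin AUC. Section 5.1 attaches no test to its between-group hypotheses and names only the within-group one. The sample size is introduced as showing an increase after MDMA. These are contradictions within the protocol, not details deferred to a later document.

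**Conclusion.** The point holds as a failure to fix the primary contrast and its sidedness. It does not hold as proof that the planned test is the wrong one. The textual inconsistency rests on no assumption.

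The consequences do rest on assumptions. The 96–100% and 73–95% figures require the SEM reading, common units, levels in place of AUC and ρ from 0 to 0.5; the conclusion that a within-group test cannot show a reduced response survives the SD reading. The power cost of sidedness (47% against 61%) exists only on the SEM reading, whereas the 5% against 2.5% directional error applies on both. A reader might also infer that the trial is underpowered. That is not established: the plan's 12 cannot be reproduced from the printed inputs without further ones, but it is not shown to be wrong.

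Because this is the trial's one confirmatory comparison, it should be settled before unblinding.

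**What to change.** In the synopsis and in section 5.1, state one primary contrast. For each subject let D = AUC(MDMA) − AUC(placebo). The contrast is mean D in patients minus mean D in volunteers, which is the group-by-treatment interaction. State H0: difference = 0, with one declared sidedness (two-sided 0.05 matches the existing not zero wording), and report the estimate with its 95% confidence interval. Label the MDMA-versus-placebo tests within each group as supportive. Reword the purpose of the sample size so that it refers to this contrast, saying whether the 30% applies to the MDMA level or to the increase and whether ± is SD or SEM. Period and baseline terms may be left to the statistical analysis plan.

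The cost is wording; no new samples or visits are needed. Two-sided testing gives less power than one-sided. Aligning the sample size may also expose a shortfall. For a 242.7 difference in D at 12 per group, power on the SEM reading is 23–60% two-sided or 34–72% one-sided (ρ from 0 to 0.7). On the SD reading, 12 per group is ample.
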